**Discussion:**

The results of this study will provide new insights into the feasibility and (cost) effectiveness of Cancer@Work, a nurse-led, stepped-care, e-health intervention for cancer patients aimed at enhancing their return to work. If proven effective, the intention is to implement the Cancer@Work intervention in usual psycho-oncological care.

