#### Economic evaluation

The economic evaluation will be conducted from a societal perspective. The following direct costs will be measured for both groups: costs to deliver the Cancer@Work intervention or costs to deliver care as usual and the following indirect costs: absenteeism, lost work productivity, lost earnings and work adjustments. The direct costs will be determined by means of the costs to deliver the Cancer@Work intervention (i.e. costs to develop and maintain the e-health intervention, average specialised nurse wage, the amount of time spent on each participant and training costs) or costs to deliver care as usual (i.e. average specialised nurse wage and the amount of time spent on addressing return to work of each participant). Absenteeism costs will be determined by means of total days on sick leave from the first day of sick leave until follow-up and on income and work productivity costs by the WLQ and on income [35, 36]. Additionally, lost earnings will be determined on the basis of the differences between income at baseline and income at follow-up. Work adjustments will be assessed by means of the cost of each work adjustment.

Direct costs will be acquired by the specialised nurses keeping track of the time spent on each participant and by the research team on keeping track of the costs to develop and maintain the Cancer@Work intervention and training costs to train specialised nurses to deliver the Cancer@Work intervention. Indirect costs will be acquired by a self-reported questionnaire completed by participants during follow-up.

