#### Economic evaluation

Direct and indirect costs will be summed for each participant. Using bootstrapping, mean differences in direct, indirect and total costs will be calculated between the control group and the intervention group [45]. Incremental cost-effectiveness ratios will be calculated by assessing the ratio between the differences in costs between the intervention and control group to the differences in return-to-work rates between the groups.

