Internet illiteracy is associated with a lower education level, while research indicates that self-management interventions might be more effective for patients with a lower educational level [44]. For that reason, we have spent extra time and effort in the development of the Cancer@Work intervention component to ensure that it was very easy to use. Moreover, one of the functionalities of the Cancer@Work intervention component is the ability for patients to contact their specialised nurse or the researcher at any time during weekdays when they have problems with the content or technical problems.

The strengths of our study design are the inclusion of patients from various hospitals from various geographical regions in the Netherlands, implementing the Cancer@Work intervention into usual care without much deviation from usual care and the follow-up of patients unwilling to participate in the trial but willing to fill in baseline and follow-up questionnaires.

A limitation of our study design is the inability of blinding patients and specialised nurses to the outcome of the randomisation. This might cause contamination between groups. Alternatives of randomisation on a patient level are cluster randomisation or a step-wedge design. A difficulty of cluster randomisation is the need for comparable clusters [48], which is not possible for this study on the hospital level as patient characteristics differ between hospitals. Likewise, a difficulty of a step-wedge design is the need for a larger sample size, starting with all clusters (i.e. hospitals) at the same time and an equal distribution of patients between clusters, which is burdening and results in complex statistical analyses [49]. For these reasons we believe that randomisation on the patient level is the best option for this study. Moreover, although specialised nurses might alter their usual care due to participation in the study, patients allocated to the control group do not have access to the Cancer@Work intervention.

If proven effective, the Cancer@Work intervention will be implemented in usual care. The e-health intervention might also be incorporated as a work-module into broader psychosocial e-health interventions for patients with cancer.

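### Development cost already spent is counted as a cost of delivering Cancer@Work and enters the cost-effectiveness ratio, with no analysis that leaves it out

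*Protocol article*

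**What the plan says.** In the protocol article, the Economic evaluation part of Assessment of the outcomes sets the viewpoint: "The economic evaluation will be conducted from a societal perspective". It then lists what counts as a cost of delivering the intervention: "costs to develop and maintain the e-health intervention, average specialised nurse wage, the amount of time spent on each participant and training costs". Usual care carries only "average specialised nurse wage and the amount of time spent on addressing return to work of each participant". The one-off and shared items are recorded as totals "by the research team on keeping track of the costs to develop and maintain the Cancer@Work intervention and training costs", whereas nurses log their time participant by participant.

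The Economic evaluation part of Statistical analysis states: "Direct and indirect costs will be summed for each participant". Mean differences in direct, indirect and total costs are bootstrapped. The ratio relates the cost difference "to the differences in return-to-work rates between the groups".

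On the use of the result, the abstract says that, given proof of effect, "the intention is to implement the Cancer@Work intervention in usual psycho-oncological care". The main Discussion says: "If proven effective, the Cancer@Work intervention will be implemented in usual care".

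The article does not say how the tracked totals become an amount per participant. It also describes no analysis without development cost.

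**The concern.** Development is listed as part of delivery, on the intervention side only. It therefore passes into the intervention arm's direct cost, into the direct and total cost differences, and into the numerator of the ratio. No described step takes it out.

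The money is already spent. The section on the content of the intervention describes development as complete, and Trial status reports recruitment from 1 September 2015. A hospital or payer deciding on adoption cannot recover that cost by declining, and society does not pay it again if the tool is adopted.

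What is at stake is the usefulness of the cost-effectiveness result, which is part of the article's declared objective. The tool would look dearer to deliver than it is. If the true cost difference is near zero, the added amount could turn an apparent saving into an apparent extra cost. Bootstrapping would not reveal this: an equal share assigned to every intervention patient has no spread between patients, so it moves the estimate and its interval without widening the interval.

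**Working it through.** **Arm size, from the plan's own figure.** Inputs from Sample size: 72 % versus 89 % return to work, power 80 %, p < 0.05 (taken as two-sided), 10 % loss. With pooled variance under the null and no continuity correction:

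n per arm = [1.96 × √(2 × 0.805 × 0.195) + 0.842 × √(0.72 × 0.28 + 0.89 × 0.11)]² / 0.17² ≈ 84.1, rounded up to 85, so 170 in total.

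This matches the stated 170. Allowing for loss, 170 / 0.90 = 189, against the stated 190. Blocks of 6, used to equalise the groups, imply 1:1 allocation, so the intervention arm is about 190 / 2 = 95.

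**How development cost enters the ratio.** Let F be the development cost and U the number of users it is spread over. The control arm carries no such item, so:

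- addition to the mean cost difference = F / U
- addition to the ratio = (F / U) / 0.17, with 0.17 = 0.89 − 0.72, the planned gain

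Each EUR 1 allocated per patient adds 1 / 0.17 = EUR 5.88 per additional return to work.

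**Dependence on the divisor, whatever F is.** Relative to U = 95, the share is smaller by 1,000 / 95 = 10.5 times at 1,000 users and by 5,000 / 95 = 52.6 times at 5,000 users. With U equal to the trial arm, doubling the arm halves the share.

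**Illustration.** The article gives no value for F or U. The values below are assumptions chosen to show a range. Each cell gives EUR per patient, then EUR added per additional return to work.

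| Assumed F (EUR) | U = 95 (trial arm) | U = 1,000 | U = 5,000 |
|---|---|---|---|
| 50,000 | 526; 3,096 | 50; 294 | 10; 59 |
| 100,000 | 1,053; 6,192 | 100; 588 | 20; 118 |
| 200,000 | 2,105; 12,384 | 200; 1,176 | 40; 235 |

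With development cost left out, the addition is zero in every column.

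**The case against.** The strongest reply is that the article never says the totals are divided over the trial's own patients. Summing costs per participant is equally compatible with a unit cost worked out over expected users and lifetime and then added to each participant's total. Divisors and amortisation periods are details an article may leave to a full protocol or economic plan that is not shown. This stands: the missing allocation rule is not itself the finding.

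A reader might go further and infer that the cost per patient and the ratio reflect the trial's size rather than the cost of the programme. The documents do not support that, for three reasons:

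- Dependence on trial size follows only if the trial arm is the divisor. That is the natural reading, since participants are the only population named, but it is not written.
- The numerator also holds nurse time, absenteeism, lost productivity, lost earnings and work adjustments, and any distortion depends on the unknown F as well as on the divisor.
- Not all the shared costs are one-off. Maintenance recurs, and use in other hospitals would need other nurses trained, so both belong in a cost of delivery. For them only the divisor matters.

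It can also be argued that counting what a programme cost to create is an accepted convention under a societal perspective. It is a legitimate supplementary figure. It does not answer the adoption question the article sets, because adoption does not cause the cost again, and the societal viewpoint does not change that.

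What the reply does not remove is the explicit listing of development as a delivery cost in the only cost-effectiveness analysis described. Any divisor leaves some of it in the main ratio, although with many users the remainder may be small.

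**Conclusion.** The point holds in a limited form. The article counts development cost already spent as a cost of delivery and carries it into each participant's direct cost, the cost difference and the ratio, with no version that excludes it. For the stated purpose of use in usual care, the ratio therefore overstates the cost of delivery.

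The size cannot be derived from the document. It is F / U per patient and (F / U) / 0.17 on the ratio at the planned gain. The trial-size dependence rests on the assumption U ≈ 95. The euro figures and the numbers of later users are illustrative only, and whether the addition matters against the indirect costs cannot be judged from the article. A different observed gain would rescale the effect on the ratio. The direction is against the intervention. The primary effectiveness analysis is untouched.

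**What to change.** Amend the economic evaluation as follows:

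1. Calculate the main cost difference and ratio without development cost, and report that cost separately as a total.
2. Keep maintenance and nurse training in the main analysis, converted to a cost per patient over a stated expected number of users and a stated lifetime of the tool.
3. Show the ratio with full development cost as a sensitivity analysis, and name the divisor used.

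No new data are needed, because the research team already tracks these totals. The change is to analysis wording plus one assumption on users and lifetime. The downside is that this assumption is uncertain and must be varied over a plausible range.

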## Method

### Content of the Cancer@Work intervention

The Cancer@Work intervention has been developed based on a non-systematic review on the use of and compliance with e-health interventions, a non-systematic review on cancer and work and on semi-structured interviews with experts, cancer survivors, occupational physicians and supervisors. Development of the nurse-led, stepped-care, e-health intervention Cancer@Work has been described extensively elsewhere [25].

The Cancer@Work intervention is an e-health intervention blended with care from a specialised nurse of the treating hospital or another care provider (e.g. social worker), depending on the local setting. For readability we will refer to this care provider as a specialised nurse. The specialised nurse will (1) answer questions, (2) monitor and supervise use of the Cancer@Work intervention, (3) provide personal feedback on assignments of the Cancer@Work intervention and (4) encourage patients to comply with the intervention. To be able to blend their care with the Cancer@Work intervention, specialised nurses have access to a special section of the e-health intervention with which they are able to (1) see whether patients have used the Cancer@Work intervention, (2) see which functionalities each patient has used, (3) evaluate the content of some of the assignments, (4) answer questions from patients, (5) send messages to patients and (6) receive support from and answers to questions from an oncological occupational physician.

The intervention comprises two steps. Whether or not the intervention goal was met with step 1 is measured based on two indicators assessed by the specialised nurse: (1) no return to work and/or (2) problems experienced upon returning to work. If either indicator is affirmative, patients will enter step 2.

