### Usual care in the Netherlands

Currently work-related issues are not structurally addressed as part of cancer (survivorship) care in the Netherlands. However, it is becoming more common to discuss this issue with a care provider at the hospital or to receive support by a reintegration office specialised in patients with cancer.

All sick-listed employees should have an occupational physician who should legally advise them about return to work according to the blueprint of evidence-based guidelines of the Dutch Association of Occupational Physicians [31]. The Improved Gatekeepers Act covers sick leave in the Netherlands and is in force during the first 2 years of sick leave. The act states that a sick-listed employee cannot be discharged and receives at least 70 % of his/her wage. The Improved Gatekeepers Act states that employers and sick-listed employees are together responsible for work resumption, which means that both parties can be sanctioned.

In the Netherlands, the social security system also provides a safety net for sick-listed workers without an employment contract according to the Improved Gatekeepers Act. Application of the Act is the same, except that these workers do not have an employer/workplace to return to. Sick-listed workers without an employment contract receive 70 % of their last daily wage during the first 2 years of sick leave. The Dutch Social Security Agency pays for the sick leave, is responsible for executing obligatory occupational health actions and should facilitate work resumption.

Self-employed persons can be privately insured against sickness absence, but most are uninsured because of the high costs. If a person is privately insured, it depends on the insurance policy as to when someone receives a supportive income, how much this supportive income is and whether or not he/she receives sickness absence counselling and vocational rehabilitation guidance.

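### Nurse time is worded differently in the two arms, the time log does not separate return-to-work time, and the occupational physician who supports the nurses is not in the cost list

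*Protocol article*

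**What the plan says.** All of this is in the protocol article.

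- **Perspective** (Assessment of the outcomes, Economic evaluation): "The economic evaluation will be conducted from a societal perspective".
- **Cancer@Work arm** (same section): the governing phrase is "The direct costs will be determined by means of the costs to deliver the Cancer@Work intervention". The components follow after *i.e.*: "costs to develop and maintain the e-health intervention, average specialised nurse wage, the amount of time spent on each participant and training costs".
- **Usual-care arm** (same sentence, also after *i.e.*): "average specialised nurse wage and the amount of time spent on addressing return to work of each participant".
- **Recording** (next paragraph): "Direct costs will be acquired by the specialised nurses keeping track of the time spent on each participant". The research team tracks development, maintenance and training costs. The instruction for nurses is not split by arm or by purpose of contact.
- **Physician** (Content of the Cancer@Work intervention): through their own section of the platform, nurses can "receive support from and answers to questions from an oncological occupational physician". This role appears neither in the cost lists nor in the recording paragraph.
- **Use of the costs** (Statistical analysis, Economic evaluation): direct and indirect costs are summed per participant and mean differences are bootstrapped for direct, indirect and total costs. The cost difference is then divided by the difference in return-to-work rates.

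**The concern.** An incremental cost is interpretable only if the same activity is counted by the same rule in both arms and every resource that the intervention adds is counted. Here the restriction to return to work is attached to one arm only. A nurse or site team could therefore log general psycho-oncological contact for a Cancer@Work patient and leave the same contact out for a control. In addition, a resource that only the intervention uses has no cost line, although the perspective is declared societal.

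Cost-effectiveness is part of the trial's stated objective, and the direct-cost difference is to be reported as a result in its own right. Minutes that were not logged by purpose are hard to recover later, and recruitment had been running since 1 September 2015.

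**Working it through.** **1. The plan's own figures.** The document states no cost or cost-effectiveness figure, so there is none to reproduce. The only number needed is the planned difference in return-to-work rates, 0.89 − 0.72 = 0.17 (Sample size). It comes from a calculation that reproduces. With a two-sided alpha of 0.05 (sidedness is not stated), 80% power, pooled variance and no continuity correction, the result is 85 per arm, 170 in total, with 80.4% power. Then 170/0.90 = 189, against the stated 190. Nothing below changes these figures.

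**2. The nurse-time wordings compared.** Let *w* be the hourly nurse cost and *G* the general contact hours per patient. Let *R*₁ and *R*₀ be the hours of return-to-work support (including Cancer@Work tasks) in the intervention and control arms.

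- Reading A, both arms limited to return to work: difference = *w*(*R*₁ − *R*₀). This is like for like.
- Reading B, intervention time unrestricted and control time restricted: difference = *w*(*R*₁ + *G* − *R*₀). This exceeds A by *wG*.
- Reading C, the log followed literally in both arms: difference = *w*(*R*₁ + *G* − *R*₀ − *G*). *G* cancels on average if general contact is equal in the two arms, but this is not the control-arm cost that the list defines.

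The text allows all three. Under none of them does the log as worded yield the restricted control minutes that the usual-care list calls for.

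**3. The physician.** If *h* physician hours per intervention patient at rate *r* are not costed, the cost difference is too low by *hr*.

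**4. Effect on the ratio.** Shift = (*wG* − *hr*) / 0.17 per extra return to work, with *wG* present only under reading B. The following values are assumptions, not in the document: *w* = EUR 30 to 50, *G* = 0 to 4 h, *r* = EUR 100, *h* = 0 to 1 h.

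- Nurse term alone: at most 4 × 50 = EUR 200 per patient; 200/0.17 = EUR 1,176. Range EUR 0 to +1,176.
- Physician term alone: at most 1 × 100 = EUR 100 per patient; 100/0.17 = EUR 588. Range EUR 0 to −588.
- Both together can cancel: 1 h × EUR 50 − 0.5 h × EUR 100 = 0.
- Or leave either sign: 2 h × 30 − 1 h × 100 = −40, a shift of −EUR 235; 2 h × 50 − 0.25 h × 100 = +75, a shift of +EUR 441.

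**The case against.** A reader might infer that the plan charges all nurse time to Cancer@Work and only work-related time to usual care. The text does not say so. The unrestricted phrase stands under the costs of delivering Cancer@Work, and the nurse's listed tasks all serve an intervention aimed at return to work. Usual care is standard psycho-oncological care, so a restriction is needed there to make the arms comparable. On that natural reading (A) the definitions agree. This stands as an answer to any claim of a deliberate unequal rule. It does not repair the logging instruction, which carries no such limit for either arm.

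A reader might also infer that work support given to controls by other hospital staff goes uncounted, because the usual-care section notes that "it is becoming more common to discuss this issue with a care provider at the hospital". That is weak. The article uses the term specialised nurse for other care providers too, such as a social worker. Under Contamination, follow-up questionnaires ask about co-interventions and about work support received by controls. Such support is monitored, though the article does not say that it is costed.

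On the physician, it can be said that the support runs through the platform and may be inside the maintenance cost, and that itemised unit costs belong in a fuller document. The text does not settle the former. On the latter, the article does give a list, worded as complete, and this resource is not named in it. The occupational physician whom sick-listed employees have under Dutch usual care is a different role and does not fill the gap.

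Finally, the sums may be small beside absenteeism and lost productivity. At an assumed EUR 2,500 a month and 260 working days a year, 2,500 × 12/260 is about EUR 115 per day, so even EUR 200 is under two days of sick leave. That holds for total costs and the ratio. It does not hold for the direct-cost difference, which is reported separately.

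**Conclusion.** The point holds as an inconsistency that leaves room for unequal costing, together with one intervention resource that has no named cost line. It does not show that the arms will be costed unequally. The nurse-time effect depends on reading B being applied in practice. The physician effect does not depend on how nurse time is read, but it presumes that the support is not already inside the platform cost. The euro ranges rest entirely on assumed wages and hours and on the planned 17-point difference. Because the two effects work against each other and no inputs are given, neither a net direction nor a net size can be stated. The matter is confined to the economic evaluation and is worth correcting because the correction is cheap.

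**What to change.** 1. Define nurse or care-provider time once, for both arms, as time spent on return-to-work support. In the intervention arm this includes Cancer@Work tasks such as feedback on assignments and supervision of use. General psycho-oncological contact is then left out of both arms.
2. Reword the logging instruction to match, and use the same form for every participant whichever arm they are in.
3. Record the oncological occupational physician's time in supporting nurses and add it as a direct cost of Cancer@Work. If it is already paid for within platform maintenance, say so, to avoid counting it twice.
4. For participants logged before the change, state which definition their entries followed.

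The cost is slightly more logging and one extra cost line. The primary outcome, its analysis and the planned 190 patients do not change.

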### Sample size

On average, we will include cancer patients at 6 weeks or 42 days after diagnosis, and the follow-up time for the primary outcome return to work will be 12 months after inclusion, hence 12 months and 42 days after diagnosis. Earlier studies in our hospital showed that return to work for patients with various cancer types was 64 % at 12 months of follow-up from diagnosis [28]. In addition, earlier studies in our hospital showed that return to work in the first 42 days is around 8 % [28]. Therefore, the return to work for the control group was set at 64 % + 8 % = 72 %. In a study of Nieuwenhuijsen et al. [29], an intervention group of 35 radiotherapy patients received a supportive work-related intervention in a hospital. Time between diagnosis and the end of treatment was a median 42 days. Return to work was measured between the end of treatment and work resumption and was 89 % after 12 months. Therefore, the return to work for the intervention group in our intervention was also set at 89 %.

Based on our earlier studies on consecutive cancer patients, a power analysis indicated that we should include a total of 170 patients with a follow-up of 1 year after inclusion to indicate a difference of 89 % return to work in the intervention group versus a 72 % return-to-work rate in the control group, with a power of 80 % and *p* < 0.05. Accounting for 10 % loss to follow-up, 190 patients should be included.

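### Costing absence and WLQ loss on income, with no covariate stated for the cost difference, adds avoidable noise to an otherwise unbiased cost comparison

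*Protocol article*

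**What the plan says.** All references are to the protocol article.

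- **Assessment of the outcomes, Economic evaluation.** Absenteeism cost is built from total sick-leave days and "on income and work productivity costs by the WLQ and on income". No standard or average wage is named for patients, whereas nurse time is priced at an average nurse wage. Lost earnings are a separate item, taken from "differences between income at baseline and income at follow-up", so income is collected at baseline. Indirect costs come from participants' own questionnaires.
- **Statistical analysis, Economic evaluation.** Costs are added up per participant, and then: "Using bootstrapping, mean differences in direct, indirect and total costs will be calculated between the control group and the intervention group". No covariate is mentioned. The cost-effectiveness ratio divides this cost difference by the difference in return-to-work rates.
- **Effectiveness secondary parameters.** The only stated covariate adjustment is for Cox models of time to return to work, and only for prognostic characteristics that differ significantly at baseline.
- **Prognostic and descriptive characteristics.** Income is listed as descriptive, not prognostic, so that rule would not reach it even if it applied to costs.
- **Randomisation, blinding and treatment allocation.** The strata are hospital department and age (cut-off 50). Income is not one of them.
- **Sample size.** "190 patients should be included", which is about 95 per arm.

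**The concern.** If lost time is priced at own pay, each patient's absence cost is days lost multiplied by pay. Pay varies between patients, is largely fixed before randomisation and is not balanced by design. Two arms that lose the same number of days will still differ in cost if one happens to contain more high earners. That gap carries over roughly in proportion to absence and WLQ costs, and from there into the numerator of the cost-effectiveness ratio.

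What is at stake is precision. The sample size was set on return to work and not on cost, so the cost comparison has no planned precision of its own. The covariate that would remove much of this noise is already being collected, and the stated estimator does not use it.

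**Working it through.** **1. Arm size.** Inputs from the Sample size section: "89 % return to work in the intervention group versus a 72 % return-to-work rate in the control group". The same section sets power at 80%, the significance level at 5% and expected dropout at 10%. Two-sided test of two proportions, pooled variance under the null, no continuity correction, mean proportion 0.805:

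n per arm = [1.96·√(2·0.805·0.195) + 0.842·√(0.72·0.28 + 0.89·0.11)]² / 0.17² ≈ 84.1, rounded up to 85.

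The total is 170, as stated ("we should include a total of 170 patients"). With 10% loss, 170/0.9 = 188.9, which is 189 against the stated 190. The figure reproduces, and about 95 per arm is right.

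**2. Chance gap in mean income.** The article gives no income spread, so its coefficient of variation (CV) is assumed. The 95% half-width, as a share of mean income, is 1.96·CV·√(2/95), with √(2/95) = 0.1451.

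| Assumed income CV | 95% chance gap |
|---|---|
| 0.30 | ±8.5% (about 9%) |
| 0.45 | ±12.8% (about 13%) |
| 0.60 | ±17.1% (about 17%) |

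**3. Why adjustment helps.** Let cost = income × days, with the two independent and CVs a (income) and b (days). Relative to the squared mean cost, the per-patient variance is:

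- unadjusted: a² + b² + a²b²
- after regression on income: b² + a²b²
- at one common wage: b²

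The SE of the arm difference is √(2·variance/95). With assumed a = 0.5 and b = 0.6:

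- unadjusted: √(2·0.70/95) = 12.1% of mean cost
- adjusted for income: √(2·0.45/95) = 9.7%
- common wage: √(2·0.36/95) = 8.7%

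A simulation of 20,000 trials with no effect on days gave the same three values. Its mean error was about zero. Over income CVs of 0.3 to 0.7 and days CVs of 0.4 to 0.8, the 5% test rejected in 4.9% to 5.4% of trials. There is therefore no bias and no loss of validity.

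**4. Size in a trial-like scenario.** Assumed: 190 versus 160 days absent, SD 110, limited to 0–365; log-normal income independent of days; 95 per arm. SEs are in days of mean pay.

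| Income CV | SE unadjusted | SE adjusted | Variance ratio |
|---|---|---|---|
| 0.30 | 17.2 | 15.3 | 1.26 |
| 0.45 | 19.7 | 15.6 | 1.60 |
| 0.60 | 22.5 | 16.8 | 1.80 |

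Repeat simulations gave ratios of 1.24–1.25, 1.52–1.57 and 1.80–1.96, so about 1.25 to 1.9 is a fair range. In this scenario the true difference is a saving. The chance that the estimate shows the wrong sign is about 6–12% unadjusted and 4–6% adjusted.

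**5. Less favourable assumptions, same scenario.** Variance ratios at income CV 0.30, 0.45 and 0.60:

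- income–absence correlation −0.2: 1.09, 1.22, 1.40
- income–absence correlation −0.3: 1.04, 1.14, 1.32
- baseline income recorded at 70–100% of true pay, and as zero for 15% of patients: 1.05, 1.22, 1.35

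The gain shrinks to about 1.05 to 1.4 but does not vanish.

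**The case against.** **A reader might infer bias**, with income differences passing for an effect of the intervention. The documents do not support that. Allocation is randomised, so the unadjusted difference is right on average. Costs are summed per participant before bootstrapping, so resampling patients carries the income variation into the interval. Chance imbalance of this kind affects any unstratified covariate. This objection stands in full and limits the point to precision.

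**The article is condensed.** It says only income, not own income, and mean differences need not mean unadjusted ones. A fuller plan could name a wage or a covariate. This stands in part. Own pay is a strong inference (self-reported income, per-participant sums, an average wage named only for nurses) but still an inference. Nor does the article rule out adjustment. It does, however, state both the valuation basis and the estimator, so the suggestion improves a stated method and does not complain of missing detail.

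**Own-pay valuation is legitimate** and compatible with the societal perspective. This stands, which is why the common wage is proposed only as a sensitivity analysis.

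**The gain depends on assumptions.** The subgroup plan links physically heavy work to a high risk of not returning. If such jobs pay less, income and absence correlate negatively. Patients enter on sick leave, when employees may receive as little as 70% of wage and most self-employed people are uninsured, so recorded baseline income may understate pay. Both cases reduce the benefit, as the working shows. Stratification by age and department may also balance income a little.

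**Not all indirect cost is time multiplied by pay.** Work adjustments are priced individually, and lost earnings are a within-person change. This stands: the figures above concern the absence cost, and the income mechanism applies to absence and WLQ loss only.

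**Conclusion.** The point holds as a matter of efficiency in a secondary analysis. As stated, the cost comparison is unbiased with a valid interval, but it is noisier than it needs to be. Under the favourable assumptions (income CV 0.30 to 0.60, income independent of days, income well recorded), the unadjusted variance is about 1.25 to 1.9 times the adjusted one. Under the harder assumptions it is about 1.05 to 1.4 times. Income spread, days absent and their SD, the correlation and the recording error are all assumed, since the article gives none of them. Most of the uncertainty, which comes from days absent, would remain after adjustment. The primary outcome and the sample size are not affected.

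**What to change.** In Statistical analysis, Economic evaluation, state that the cost difference within each bootstrap sample is estimated from a regression of cost on arm and baseline income. The abstract places the baseline questionnaire before randomisation, so baseline income is a proper covariate. Add a sensitivity analysis that values absence and WLQ loss in both arms at one common wage, for example the trial mean, so that those components reflect time lost only. In Assessment of the outcomes, Economic evaluation, say explicitly whose income is used for the main valuation.

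The cost is one extra regression term and a few lines of wording and code, with no new data and no change to trial conduct. The downside is that the common-wage sensitivity analysis does not reflect individual pay.
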